### Recruitment

In order to achieve adequate participant enrolment, an announcement regarding the study is built into the EHR system. When the physician initiates a blood culture request in the EHR for an adult patient in the ED, a pop-up notification will automatically appear. This pop-up briefly outlines the study and presents both inclusion and exclusion criteria. If the patient provides permission to receive information about the study, the study team will be alerted and will provide the patient with additional information and obtain informed consent.

### Outcomes

The primary objective is to investigate whether using a machine learning-based blood culture prediction tool is non-inferior to current practice regarding 30-day all-cause mortality. All secondary outcomes are described in table 2. Model performance will be evaluated using the AUROC, Area Under the Precision-Recall Curve (AUPRC) and calibration for the model in the complete study population and subgroups based on comorbidities. This will be assessed every 3 months so model performance over time can be guaranteed. The model will also continue to undergo prospective validation in the background of the EHR. Additionally, patient-reported outcomes will be included to determine if the model also influences patient-reported outcome measures such as side effects from antibiotics and quality of life. For assessment of quality of life, the EuroQol 5-Dimension 5-level (EQ-5D-5L) Questionnaire^12^ will be filled out at baseline and 3 months. Lastly, a cost-effectiveness analysis will be performed using cost questionnaires based on the iMTA Medical Consumption Questionnaire (iMCQ) and iMTA Productivity Cost Questionnaire (iPCQ).^13^ A timeline visualising data collection is shown in table 3.

**Table 3 T3:** Data collection timeline

Allocation	Enrolment	Allocation	Baseline	During admission*	3 months after baseline
Eligibility screen	X				
Informed consent	X				
Allocation		X			
Vital parameters			X		
Lab values			X		
Quality of life (according to EQ-5D-5L)			X		X
Cancelling blood culture^A^			X^A^		
Admission rates			X		
Mortality				X	X
Patient-related outcomes^B^			X	X	X
Diagnostics related outcomes			X	X	X
Therapy-related outcomes			X	X	X
Model related outcomes			X	X	X
Cost questionnaire					X

A: Only in intervention group when predicted probability of positive blood culture is <5%. B: See table 2.

*Not applicable to all participants.

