### Model development and validation

This segment features a summary of the model development, more detailed descriptions have been published previously.^9 10^ For the development of the model data from the VUmc was split into a training (80%) and a test set (20%), stratified by blood culture outcomes. Missing data were imputed by medians. The model was trained on the training set and subsequently validated in the VUmc test set, and three other hospital datasets (AmsterdamUMC location AMC, Zaans Medisch Centrum (ZMC, Zaandam, The Netherlands) and Beth Israel Deaconess Medical Center (BIDMC, Boston, Massachusetts, USA)). These hospitals differ in size and population, comprising two tertiary teaching hospitals and one secondary care hospital in the Netherlands, along with one hospital dataset from the USA. Part of the data was gathered during the COVID-19 pandemic, but this did not affect its performance. The model contains 49 variables, namely age, sex, 6 vital sign measurements and 18 laboratory tests. Additionally, indicator variables of the laboratory tests were included. Figure 1 shows the 20 most important variables. The area under the receiver operating characteristic (AUROC) curves in the various validation cohorts ranged between 0.75 and 0.81. A prospective validation was also performed, integrating the model into the EHR of VUmc, showing an AUROC of 0.76. With the threshold for blood culture analysis set at 5%, analyses could be avoided at approximately 30%.

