### Study design

This study will be a multicentre randomised controlled non-inferiority trial. Participants will be randomised into an intervention and control arm. In the intervention group, the blood culture prediction model is used to predict the probability of a positive blood culture in the patient. The model will start predicting when sufficient variables are available in the EHR. A new prediction will be made every 20 min until 3 hours have passed since check—in of the patient in the ED. The predictions made by the model will be shown to the physician after randomisation in a dashboard integrated into the EHRs. The blood culture analysis will be cancelled if the probability of a positive culture is less than 5%. This will be done manually by the study team. If the probability is over or equal to 5%, the blood culture will be analysed as per standard practice. In the control group, all patients will have their blood cultures analysed. The study design is summarised in figures 2 and 3. Patients will be randomised within the EHR system, to ensure that physicians cannot be influenced in their treatment decisions by seeing the score before the patient is included. The first patient was included in February 2024. Follow-up of the last patients is expected in February 2027.

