### Sample size calculation

An analysis of 5907 unique ED visits with blood culture sampling in Amsterdam UMC showed a 30-day mortality rate of 7.6%, a hospital admission rate of 67.4% and an average length of stay in the hospital of 6.7 days. Based on these numbers, the sample sizes with a relative non-inferiority margin of 1.25 for the rates and 1 day for the length of stay were calculated. The sample sizes were calculated by a statistician based on a one-sided alpha of 5% and a target power of at least 80%. For 30-day mortality, the calculated sample size was 6066 (3033 per arm) to test non-inferiority. After inflation for a dropout rate of 20%, the final sample size is 7584 (3792 per arm). For the secondary outcomes, described in table 2, fewer participants were needed for adequate power.

**Table 2 T2:** Overview of outcome measures

Primary outcome	30-day all-cause mortality
Key secondary outcomes	In-hospital mortality
	Hospital admission rates
	Hospital length-of-stay
Other outcome measures	
Patient-related outcomes	90-day mortality
	30-day readmission rates
	Emergency department length-of-stay in hours
Diagnostics related outcomes	Percentage of blood cultures avoided in the intervention group
	Number of blood cultures on each day of hospital stay (in admitted patients)
	Percentage of positive blood cultures in each group
	Total number of laboratory and microbiology tests in the ED
	Total number of laboratory and microbiology tests on each day of hospital stay (in admitted patients)
Therapy-related outcomes	Percentage of patients receiving antibiotics in the ED
	Duration of antibiotic therapy
	Types of antibiotics given in the ED
Model-related outcomes	Model performance (AUC) during the trial
	Model performance in subgroups: Immunocompromised patients (triple immunosuppressive therapy) Patients who had transplants

AUC, area under the operating curve; ED, emergency department.

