## Ethics and dissemination

Obtaining informed consent is of the utmost importance when working with study participants. In order to ensure that participants are well informed about the study before consenting, all potential participants will have the trial clearly explained to them by a trained member of the study team. In addition to the verbal information, a paper information brochure will be provided to each participant, see online supplemental material 1. We inform patients about the procedures and what the consequences of doing or withholding blood cultures can be, as this is the most relevant information for them. Each participant will be made aware of their right to withdraw consent at any given time. If a patient withdraws consent their data will no longer be used in the study and the study personnel will not follow them up. If the patient was in the intervention group and blood culture analysis was already cancelled, we cannot reinstate the analysis, since the material has been destroyed. Due to the nature of the study, the potential participant will get 1 hour to consider joining the study. If any change to the protocol is made the ethics review board will be notified and will have to give permission. If the changes are relevant to the participants, they will receive additional information regarding the changes made.

10.1136/bmjopen-2024-084053.supp1Supplementary data

Research results will be published in peer-reviewed journals approximately 1 year after the trial has ended. This will give the research team sufficient time for statistical analyses.

This study will be conducted according to the principles of the Declaration of Helsinki and in accordance with the Medical Research Involving Human Subjects Act, General Data Privacy Regulation and Medical Device Regulation. The study was approved by the Amsterdam University Medical Center’s medical ethics review committee with number 22.0567. The trial was registered at Clinicaltrials.gov (NCT06163781).

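### Model performance is planned for the whole trial population, but about 15% of participants, selected by the score itself, will have no culture result, so an unadjusted pooled AUROC is about 0.02 too low

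*Protocol article*

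**What the plan says.** Under Outcomes, the article plans to evaluate AUROC, AUPRC and "calibration for the model in the complete study population and subgroups based on comorbidities". It adds: "This will be assessed every 3 months so model performance over time can be guaranteed". Continued background validation in the EHR is mentioned as a further activity.

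Under Study design, for the intervention arm: "The blood culture analysis will be cancelled if the probability of a positive culture is less than 5" per cent. For the other arm: "In the control group, all patients will have their blood cultures analysed". Under Ethics and dissemination, on a patient who withdraws after cancellation: "we cannot reinstate the analysis, since the material has been destroyed".

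Model development and validation gives the expected extent: "With the threshold for blood culture analysis set at 5%, analyses could be avoided at approximately 30" per cent. It also gives the pre-trial benchmark, obtained by "integrating the model into the EHR of VUmc, showing an AUROC of 0.76".

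Table 2 lists model performance among the other outcome measures, together with "Percentage of positive blood cultures in each group", for which no denominator is given.

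**The concern.** AUROC needs a score and a reference result for every patient analysed. Here the reference result is missing because of the score: in one arm, everyone below the threshold goes uncultured. This is partial verification. The population named for the analysis cannot be complete, and the two simplest ways round the gap err in opposite directions. Dropping uncultured patients removes many easily ranked negatives and lowers AUROC. Counting them as negative relabels the positives among them and raises it.

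The trial figure would then not be comparable with the pre-trial 0.76, which came from running the model in the EHR before any culture was cancelled. An unchanged model could look worse in the trial than in any validation cohort. The percentage of positive cultures raises a related, smaller matter: the direction of the difference between arms depends on the denominator.

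**Working it through.** **The plan's own figure.** The article states no number for the model-performance analysis. The sample size, which supplies the 3792 used below, reproduces. A Farrington-Manning non-inferiority test for a ratio of proportions, with 7.6% mortality in both arms, margin 1.25, one-sided alpha 0.05 and power 0.80, gives 3032.2, so 3033 per arm. Then 3033/0.8 = 3791.25, so 3792 per arm and 7584 in total.

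**Participants without a result.** 0.30 x 3792 = 1138, and 1138/7584 = 15%. On the 3033 per arm before dropout inflation, 0.30 x 3033 = 910 of 6066, also 15%.

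**Effect on AUROC and AUPRC.** From the article: 30% below 5%, AUROC 0.76 (range 0.75 to 0.81), 1:1 allocation. Assumed: a calibrated model with logit(p) = mu + s·Z and Z standard normal.

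- mu = ln(0.05/0.95) - s·Φ⁻¹(0.30) puts 30% below 5%. Solving for AUROC 0.76 gives s = 1.061. The implied positive rate is 11.9% overall and 2.93% below the threshold.
- Each score gets a weight w equal to the fraction cultured. Below 5%, w = 1 in controls, 0.5 when arms are pooled and 0 in the intervention arm. Above 5%, w = 1 throughout.
- AUROC is the probability that a positive drawn with weight w·p outranks a negative drawn with weight w·(1-p).

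| True AUROC | Pooled, cultured only | Intervention arm, cultured only | Pooled, cancelled coded negative |
|---|---|---|---|
| 0.75 | 0.731 | 0.698 | 0.774 |
| 0.76 | 0.741 | 0.708 | 0.782 |
| 0.81 | 0.789 | 0.754 | 0.825 |

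A binormal score with AUROC 0.76 and a positive rate anywhere from 1% to 15% (the range in the Introduction) gives 0.741 to 0.742 pooled and 0.708 to 0.713 in the intervention arm. The size therefore does not hinge on one score distribution. AUPRC at true AUROC 0.76 moves from 0.326 to 0.334 pooled and 0.341 in the intervention arm.

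**Calibration.** Whether a culture is analysed depends only on score and arm, and arm is randomised. The observed rate at a given score is therefore unbiased among cultured patients. In a simulation of 4 million patients:

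- A calibrated model keeps slope 1.00 and observed/expected 1.00.
- In a scenario with understated low risks, observed/expected below 5% is 1.93 with or without the cancelled patients.
- Whole-sample summaries shift only if the model is miscalibrated: observed/expected from 1.21 to 1.18 in one scenario, slope from 0.84 to 0.90 in another.

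Negative coding is different. About 1138 x 0.0293 = 33 positives would be expected below 5% in each arm. Setting those in the intervention arm to zero halves the pooled rate there, from 2.93% to about 1.5%, and lowers overall observed/expected to 0.963.

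**Percentage positive, with no true difference between arms.** Controls: 11.9%. The stratum below 5% contributes 0.30 x 2.93% = 0.88 percentage points. The intervention arm therefore shows 11.89 - 0.88 = 11.0% per randomised participant, or 11.01/0.70 = 15.7% per analysed culture: lower than controls on one denominator, higher on the other.

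**Performance of the remedy.** Weight 2 for controls below 5% restores w = 1 throughout, so AUROC returns to 0.76. For a three-monthly sample, assume even accrual over 36 months: 7584/12 = 632. Root mean squared error in simulation is then about 0.037 for unadjusted pooling (bias -0.02, SD 0.031), 0.041 for controls alone and 0.034 for weighted pooling. At 7584 patients it is 0.021 for unadjusted and 0.010 for weighted pooling.

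**The case against.** **Missing reference results are analysis-plan detail, and the phrase about the population only contrasts overall with subgroups.** This is fair as to the remedy. But the article does name a population, and its own intervention makes that population incomplete. An analyst following it with no adjustment gets a wrong number.

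**Calibration is not distorted.** This stands for calibration plots, the form named under Statistical analysis. A reader might infer that partial verification spoils every metric. For plots in cultured patients the loss is precision below 5%, not validity.

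**Nothing says cancelled cultures are counted as negative.** This stands. A reader might infer that the plan hides missed bloodstream infections, but that needs a coding step the article never states. The upward figures show only what such coding would do.

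**The three-monthly review is not a safety guarantee for the threshold.** This stands. The text speaks of model performance; safety oversight lies with the monitoring board, the mortality review after 2850 patients and adverse-event monitoring.

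**The offset creates no trend.** With a stable case mix it is roughly constant from the first quarter, so it would not mimic drift between quarters, and it is smaller than quarterly noise. What remains is the comparison with pre-trial benchmarks, and the final analysis, where the bias exceeds sampling error. The point that a control-only analysis is noisier per quarter also stands; weighted pooling answers it.

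**Higher yield per analysed culture is an intended effect, and the article does not define 'positive'.** Both stand. It cannot be concluded that the yield comparison is pure artefact, or that it mixes pathogens with contaminants.

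**Background validation runs in parallel.** True, but it is presented as additional and does not replace the trial-population analysis.

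**Conclusion.** The point holds for AUROC. Unadjusted pooling of cultured patients biases it down by about 0.02 (0.76 to 0.74), and the intervention arm alone by about 0.05. Negative coding, were it used, would bias the pooled figure up by about 0.02 and halve the apparent positive rate below 5%. AUPRC shifts only slightly, and calibration plots in cultured patients remain valid.

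The documents do not support reading this as a threat to patient safety or to the trial's main conclusion. It concerns other outcomes, leaves the primary mortality analysis and sample size untouched, and can be repaired fully because the control arm is cultured throughout. Severity: should be fixed.

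Assumptions: 30% below 5% in both arms, full adherence to cancellation, no substitute early culture, and a logit-normal or binormal score. The 11.9% positive rate is implied by the model, not stated in the article. Rescoring every 20 minutes was not modelled.

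**What to change.** For both the final and the three-monthly reports, including subgroups, state that:

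- AUROC and AUPRC are estimated from cultured patients in both arms, with weight 2 for control patients scoring below 5% and weight 1 otherwise, or in the control arm alone;
- calibration below 5% and the positive rate below 5% are reported from controls;
- cancelled cultures are treated as unverified and never coded as negative;
- the percentage of positive cultures is given per randomised participant as well as per analysed culture.

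The weight of 2 follows from 1:1 allocation. If some cultures below 5% are analysed despite the rule, use the inverse of the observed fraction cultured in that stratum instead.

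The cost is wording and a small change to the reporting code. Intervals for AUROC become somewhat wider: the quarterly SD rises from about 0.031 unadjusted to 0.034 weighted, or 0.041 with controls alone. No data collection, sample size or trial procedure changes.

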### Data collection and management

The data underlying this study, including the outcome measures such as mortality and admission rates, will be automatically extracted from the EHR system into an electronic data capture system (Castor EDC). The questionnaires regarding patient-reported outcomes and cost–benefit analysis will subsequently be sent out digitally through the EDC system. The data will be stored for 15 years, in agreement with local regulations and with consent. Data management and monitoring will be performed by the study team. Additionally, a monitor from the local independent clinical monitoring centre will monitor the data and perform data validation checks. Participant data underlying the results of this study can be shared. The data can be requested following publication of this work. The data can be shared with researchers on reasonable request, which is allowed under local privacy regulations. Proposals should be directed to the corresponding author and requestors will need to sign a data access agreement.

### Safety, adverse events and monitoring

Adverse events will be monitored by the investigators, including device-related adverse events. Serious adverse events will be reported within a maximum of 15 days to the local authority, and an annual safety report will be submitted to the local authorities. Examples of possible adverse events include delayed appropriate antibiotic treatment, hospital readmission or prolonging of hospital stay. The study risk was assessed using the Nederlandse Federatie van Universitair Medische Centra (NFU) risk classification and classified as moderate risk.^14^ The study has its own data safety monitoring board (DSMB) consisting of clinicians, a statistician and an epidemiologist, independent of the study team. The DSMB will meet before the first year of the study ends and once a year during the study period. During the study period, the DSMB will be supplied with an interim analysis and will advise the study team based on these results. A meeting will be held to evaluate mortality after 2850 patients have completed the trial. Additional meetings may be requested based on trial events. At least 2 weeks before each meeting, the DSMB will receive reports regarding data quality, recruitment and patients’ safety. The DSMB will report back to the principal investigator regarding any advice they may have. Additionally, the study will be monitored by an independent clinical trial monitoring committee, which performs quality checks on the data and regular on-site auditing.

### Allocation and randomisation

Participants will be randomly assigned to either the intervention or control group with a 1:1 allocation through a validated computer-generated random number within the EHR system. This will be a simple randomisation without stratification. Randomisation will occur automatically after consent and after blood cultures have been ordered. Physicians caring for a patient in the control group will not see any algorithm predictions. Physicians caring for a patient in the intervention group will be able to see the algorithm prediction. Due to the nature of the intervention, neither participant nor staff can be blinded to the allocation.

### Statistical analysis

We will carry out a per-protocol analysis. The primary outcome, the 30-day mortality rate, will be compared between the groups using a non-inferiority test for the ratio of two proportions. This will be a one-sided test with a significance level of 0.05. Additionally, we will do a multivariable analysis of the primary and key secondary outcomes to adjust for potential effect of age, Charlson Comorbidity Index, use of immunosuppressive medication, Modified Early Warning Score and resuscitation status. Similar tests will be performed for in-hospital mortality rate and the hospital admission rate. The hospital length-of-stay will be analysed as a continuous variable and a non-inferiority test for the differences between the two means will be used. The test statistic to be used is a one-sided T-test with a significance level of 0.05. The model-related outcomes will be assessed using an area under the curve and calibration plots. Baseline characteristics will be presented using descriptive statistics, without statistical testing for differences, since this is a randomised trial.

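### Per-protocol is the only analysis set named for the mortality non-inferiority test, although departures from the cancellation rule can occur in the intervention arm alone

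*Protocol article*

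**What the plan says.** All references are to the protocol article.

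- **Statistical analysis.** The section begins: "We will carry out a per-protocol analysis". The primary outcome, 30-day mortality, "will be compared between the groups using a non-inferiority test for the ratio of two proportions", and "This will be a one-sided test with a significance level of 0.05". The multivariable analysis that follows adds a covariate-adjusted model, not a second population. No analysis of everyone randomised, by allocated arm, is mentioned anywhere in the article.
- **Study design.** In the intervention arm, study staff cancel the culture by hand when the predicted probability is under 5%. For the other arm: "In the control group, all patients will have their blood cultures analysed".
- **Allocation and randomisation.** Physicians see the prediction in the intervention arm and not in the control arm. The trial is open-label.
- **Model development and validation.** At the 5% threshold, about 30% of analyses could be avoided.
- **Sample size calculation.** The need is 3033 per arm, raised to 3792 per arm (7584 in total) for 20% dropout.
- **Ethics and dissemination.** "If a patient withdraws consent their data will no longer be used in the study and the study personnel will not follow them up". This applies to both arms.

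**The concern.** The trial makes a safety claim: withholding a test does not raise mortality by more than a ratio of 1.25. Randomisation supports that claim only if the groups compared are the groups that were randomised.

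A per-protocol set removes patients for events after allocation. Here one such event, a culture analysed despite a score under 5%, can happen only in the intervention arm. A control patient with the same score gets usual care and stays in. If the excluded patients differ in prognosis from the rest of their arm, the arms stop being comparable, and adjusting for the listed covariates does not reliably restore the balance. Other exclusions, such as eligibility violations or withdrawals, can occur in either arm.

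With one analysis set, there would be no as-randomised result against which to judge the effect of these exclusions.

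**Working it through.** **Inputs from the article.** Reference 30-day mortality 7.6%, margin 1.25 as a ratio, one-sided alpha 5%, power at least 80%, 3033 per arm before and 3792 per arm after 20% dropout, and about 30% of patients below the threshold.

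**1. The plan's own figures.** Take the Farrington-Manning score test for a ratio with p = 0.076 in both arms and margin M = 1.25. The null-restricted rates are 0.0844 and 0.0675, so the null variance term is 0.1756. The alternative variance term is p(1−p)(1+M²) = 0.1799. Then

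n = (1.645·√0.1756 + 0.842·√0.1799)² / (0.076 − 1.25·0.076)² = 3032.2, so 3033 per arm.

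Dropout: 3033 / 0.80 = 3791.25, so 3792 per arm and 7584 in total. Both figures reproduce exactly, so the sample size is not at fault. The simpler log-ratio formula gives 3020 per arm, close enough to use below.

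**2. Power with everyone analysed as allocated.** SE = √[2(1−p)/(n·p)] and power = Φ(ln 1.25/SE − 1.645), at a true ratio of 1.0.

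- n = 3792: SE = 0.0801, power = Φ(1.142) = 87.3%.
- n = 3033: SE = 0.0895, power = Φ(0.847) = 80.2%.

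**3. The pool in which a cancellation can be missed.** 0.30 × 3792 = about 1138 intervention patients. The control arm has no counterpart. Excluding 6% of the intervention arm (about 228 patients) means a missed cancellation in one in five of that pool.

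**4. Effect of one-arm exclusion.** Let e be the share of the intervention arm excluded, and k the mortality of those excluded relative to the arm average. *Both are assumptions; the article gives neither.* The remaining intervention mortality is multiplied by f = (1 − e·k)/(1 − e), with (1 − e)·3792 patients left. The chance of declaring non-inferiority is Φ([ln 1.25 − ln(observed ratio)]/SE − 1.645).

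For e = 6% and a true ratio of 1.25 (9.5% against 7.6%):

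- k = 2: f = 0.88/0.94 = 0.936, rate 8.89%, ratio 1.170, SE 0.0780, Φ(−0.799) = 21.2%.
- k = 0.5: f = 0.97/0.94 = 1.032, rate 9.80%, ratio 1.290, SE 0.0761, Φ(−2.058) = 2.0%.

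The same steps over a range, with 3792 per arm randomised:

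| e | k | expected ratio when truth is 1.25 | false non-inferiority | power when truth is 1.0 |
|---|---|---|---|---|
| 3% | 0.5 | 1.27 | 3.2% | 82.7% |
| 3% | 1 | 1.25 | 5.0% | 86.9% |
| 3% | 2 | 1.21 | 10.8% | 93.1% |
| 6% | 0.5 | 1.29 | 2.0% | 76.8% |
| 6% | 1 | 1.25 | 5.0% | 86.4% |
| 6% | 2 | 1.17 | 21.2% | 96.7% |
| 10% | 0.5 | 1.32 | 0.9% | 67.1% |
| 10% | 1 | 1.25 | 5.0% | 85.7% |
| 10% | 2 | 1.11 | 43.2% | 99.1% |

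The k = 1 rows show that losing numbers alone does little. The damage comes from a difference in prognosis, and its sign follows k.

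**The case against.** **Per-protocol is a recognised analysis in non-inferiority trials**, because poor adherence can dilute a real difference in an as-randomised analysis. This stands as a reason to keep it, and making the as-randomised set the sole primary analysis would be partly preference. It does not justify having no randomised comparison at all.

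**The analysis plan may add a set, and the article does not define per-protocol exclusions.** Both are true. The point is limited to what the article fixes: one named set, with the primary test stated directly after it. Whether a missed cancellation leads to exclusion is an inference from the ordinary meaning of per-protocol.

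**A reader might infer that the exclusions would remove sicker patients and so favour the intervention.** The article does not support that. It describes no clinician override, and a missed cancellation could be purely logistical. Missed cancellations come only from patients the model scores as low risk for a positive culture. Their mortality may be below average, although no figure is given. The bias would then work against non-inferiority.

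**A reader might take the 20% dropout allowance as the share that per-protocol would exclude.** It is an inflation applied to both arms, not a one-arm exclusion rate.

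**A reader might count the removal of withdrawn patients' data as a consequence of choosing per-protocol.** It is a consent rule, covers both arms, and would reduce an as-randomised analysis too.

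**Conclusion.** The point holds in this form: the article rests the primary mortality conclusion on a single per-protocol set, in a design where departures from the cancellation rule can occur only in the intervention arm. Exclusions on that ground would make the comparison non-randomised.

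Neither the direction nor the size of the bias can be known from the article. Across the assumed range (3% to 10% of the intervention arm excluded, with half to twice the arm's average mortality), the nominal 5% error lies anywhere from about 1% to about 43%. Power at a true ratio of 1.0 lies between about 67% and 99%. These are illustrations of sensitivity, not forecasts. They assume 3792 per arm with no other losses, exclusions in the intervention arm only, and a log-ratio approximation. Confidence is high that an as-randomised analysis is needed, and low on how much the per-protocol result would differ from it.

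**What to change.** Amend the Statistical analysis section as follows:

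1. Add an analysis of all randomised participants by allocated arm, leaving out only those whose withdrawal of consent bars use of their data. Make it co-primary with per-protocol, and declare non-inferiority only if both meet the 1.25 limit.
2. Define the per-protocol exclusions before outcome data are seen. Do not exclude intervention patients because a culture was not cancelled. Use only exclusions that can be applied equally to controls, such as eligibility violations judged on facts fixed before allocation.
3. Report withdrawals by arm, with a bound on how far they could move the mortality ratio.

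**Cost.** This is about one paragraph of text. No larger sample is needed: the as-randomised analysis alone has 87% power with 3792 per arm and 80% if losses bring it to 3033. No alpha adjustment is needed, because both analyses must succeed. The downside is that requiring agreement is slightly stricter: joint power cannot exceed that of the weaker analysis.

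### The primary mortality test leaves out the five baseline covariates the plan itself names; making the adjusted risk ratio primary would add about 2 to 7 points of power (under assumed prognostic strength) with no extra patients

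*Protocol article*

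**What the plan says.** All references are to the protocol article.

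- **Statistical analysis.** Thirty-day mortality is to be "compared between the groups using a non-inferiority test for the ratio of two proportions", one-sided at 0.05. No covariates are attached to this test. The next step reads: "Additionally, we will do a multivariable analysis of the primary and key secondary outcomes to adjust for potential effect of age". The list goes on to the Charlson Comorbidity Index, immunosuppressive medication, the Modified Early Warning Score and resuscitation status. No model or effect measure is named for this further analysis.
- **Sample size calculation.** The trial is sized for the unadjusted comparison at 7.6% mortality with "a relative non-inferiority margin of 1.25 for the rates", one-sided alpha 5% and power of at least 80%. The result: "the calculated sample size was 6066 (3033 per arm) to test non-inferiority". A 20% dropout allowance brings this to 3792 per arm.
- **Allocation and randomisation.** "This will be a simple randomisation without stratification".

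**The concern.** The sponsor has already judged these five factors worth adjusting for, yet the analysis that decides non-inferiority does not use them. When baseline factors predict the outcome, a standardised (marginal) risk ratio estimates the same quantity as the raw ratio, against the same 1.25 margin, with smaller variance. The upper confidence bound becomes tighter without recruiting anyone.

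Planned power is at the 80% target if the full 20% dropout occurs, and unstratified randomisation means none of this prognostic variation is handled by the design. At stake is a somewhat higher chance of missing non-inferiority when it is true. The validity of the primary conclusion is not at stake.

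**Working it through.** **Inputs from the article.** Control mortality p = 0.076; margin R = 1.25; one-sided alpha 0.05; power 0.80; 3033 evaluable per arm; 1:1 allocation. A true ratio of 1 is assumed for power; the article does not state it, but it reproduces the article's figure.

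**Step 1: reproduce the sample size.** Farrington-Manning score test for a ratio, equal arms:

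n per arm = (z₀.₉₅·√V₀ + z₀.₈₀·√V₁)² / [(R − 1)p]²

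- The constrained estimates under the null are 0.08436 and 0.06749 (ratio 1.25).
- V₀ = 0.08436 × 0.91564 + 1.25² × 0.06749 × 0.93251 = 0.17557, so √V₀ = 0.41902.
- V₁ = 0.076 × 0.924 × (1 + 1.25²) = 0.17995, so √V₁ = 0.42420.
- (R − 1)p = 0.25 × 0.076 = 0.019.
- n = (1.64485 × 0.41902 + 0.84162 × 0.42420)² / 0.019² = 1.04624² / 0.000361 = 3032.2, i.e. 3033 per arm. This matches the article.
- Dropout: 3033 / 0.80 = 3791.25, i.e. 3792 per arm and 7584 in total. This also matches.

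**Step 2: power of the unadjusted test.** Power = Φ[(0.019·√n − 1.64485 × 0.41902) / 0.42420].

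- n = 3033: Φ(0.842) = 80.0%.
- n = 3792 (nobody lost): Φ(1.133) = 87.1%.

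**Step 3: gain from adjustment.** The variance of the standardised log risk ratio shrinks by about (1 − R²), where R² = Var(risk given covariates) / [p(1 − p)]. This is equivalent to an effective n of 3033 / (1 − R²). The article gives no prognostic strength, so a range of AUROC is assumed and turned into R² through a logit-normal risk distribution with mean 7.6%.

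| Assumed AUROC for death | R² | Effective n per arm | Extra per arm | Power |
|---|---|---|---|---|
| 0.70 | 0.044 | 3172 | 139 | 81.5% |
| 0.75 | 0.076 | 3283 | 250 | 82.7% |
| 0.80 | 0.124 | 3461 | 428 | 84.4% |
| 0.85 | 0.192 | 3754 | 721 | 86.9% |

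**Step 4: check by simulation.** G-computation from a logistic model was run with 6066 patients and 1500 runs per scenario. The variance ratio (adjusted to unadjusted) was 0.930, 0.868 and 0.735 at AUROC 0.75, 0.83 and 0.89; the approximation 1 − R² gives 0.923, 0.833 and 0.738. Simulated power of the adjusted analysis was 82.0%, 85.3% and 89.4%. The approximation is adequate.

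**The case against.** The strongest reply is that nothing here is wrong. The test and the sample size agree with each other, the 80% target is met, and an adjusted analysis is already planned; only its rank is in dispute. That stands, and it is why the point concerns efficiency alone.

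Other parts of the reply also stand:

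- The gain depends on an assumed AUROC. At 0.70 it is only about 1.5 points.
- Eighty per cent is a planned floor. With everyone evaluable, power is 87.1%, about what the most favourable row of the table gives.
- Table 3 lists vital parameters and laboratory values but not the Charlson index, immunosuppressive medication or resuscitation status. That these are collected is inferred from their planned use.
- Simple randomisation is not a flaw in itself. With 3033 per arm, the chance difference in a standardised covariate has a standard deviation of √(2/3033) = 0.026, and the unadjusted test's error rate already allows for it.

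A reader might go further and infer that the multivariable analysis will set a conditional odds ratio against the 1.25 risk-ratio margin. The article does not support this: it names no logistic model, no odds ratio and no margin for that analysis, and such detail is commonly left to the SAP. A reader might also want the prediction model's own score as a covariate. The article says the score is refreshed every 20 minutes for up to 3 hours after check-in and does not define which value is stored, so this cannot be required.

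None of this removes the central point: the change keeps the estimand and margin, uses covariates the sponsor chose, and needs no patients.

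**Conclusion.** The point holds as a worthwhile gain in efficiency. The primary test as written is valid and adequately sized by its own target. Replacing it with a standardised marginal risk ratio would raise power at 3033 per arm from 80.0% to between 81.5% and 86.9% for an assumed covariate AUROC of 0.70 to 0.85.

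The size of the gain rests on that assumption, on 7.6% mortality, on a true ratio of 1, and on all five covariates being available as pre-randomisation values. The reading that the trial is underpowered or its primary result invalid is not supported.

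**What to change.** Before any comparison of outcomes by arm, amend the plan as follows.

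1. Make the primary analysis the covariate-standardised marginal risk ratio for 30-day mortality. Obtain it by g-computation from a logistic model with treatment, the five named covariates at their pre-randomisation values, and hospital.
2. Declare non-inferiority if its one-sided 95% upper confidence bound is below 1.25. State the variance method.
3. Keep the unadjusted ratio test as a supportive analysis.
4. State a rule for missing covariate values, and confirm that all five covariates are recorded before randomisation.

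Margin, alpha and sample size stay as they are. The cost is a protocol and SAP amendment and modest programming. The Ethics and dissemination section requires ethics board permission for any protocol change. Timing matters: the first patient was included in February 2024, and the Safety section schedules a mortality evaluation after 2850 patients. A change made once results by arm are known would look data-driven.
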